## Methods/Design

### Study design

The present study is a randomised controlled trial (RCT) (ClinicalTrials.gov ID: NCT01374893) and is designed to be compliant with the recommendations of the Consolidated Standards of Reporting Trials (CONSORT) statement [23]. The study flow diagram is shown in Figure 1. After signing an informed consent form subjects will be randomly assigned (as explained below) to either the intervention or control group. The intervention group will perform the multi-session per day training program while the control group will receive normal hospital care. Due to the possible effect of subjects in the control group seeing subjects in the intervention group performing physical activity in addition to normal hospital care, randomization will take place in a time dependent manner. Patients admitted during four-week blocks of time will all be assigned to either the treatment or control group, with a one week period between four-week periods. The participants will be followed for the length of their hospital stay, and also with a follow-up phone interview three months after discharge to determine mortality rate at three months, number of falls since discharge, and to subjectively assess the ability to cope with ADLs using the Katz ADL score [24] and the Barthel ADL index [25].

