**Figure 1 F1:**
[figure not shown]
Study flow diagram.

All testing (at admission and discharge) will be performed in the same setting (*Hospital General Universitario Gregorio Marañón*, Madrid, Spain) and by the same investigators. The study will be performed between June 2012 and June 2013, following the ethical guidelines of the Declaration of Helsinki, last modified in 2000.

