### Study participants and selection criteria

Participants will include approximately 150 elderly people aged 75 years or older recruited from patients admitted into the Geriatrics Department of the *Hospital General Universitario Gregorio Marañón* (Madrid, Spain). Due to the length of the study it is possible a patient will be readmitted after participating in either the experimental or control group. To avoid this confounding variable, a study participant who is readmitted to the hospital during the course of the study will not be included in the study population a second time.

The inclusion criteria are:

Age: 75 years or over.

Able to ambulate, with or without personal/technical assistance.

Able to communicate.

Informed consent: Must be capable and willing to provide consent.

The exclusion criteria are:

Duration of hospitalization < 72 hours

Any factor precluding performance of the physical training program or testing procedures as determined by the attending physician. These factors include, but are not limited to the following:

Terminal illness.

Myocardial infarction in the past 3 months.

Not capable of ambulation.

Unstable cardiovascular disease or other medical condition.

Upper or lower extremity fracture in the past 3 months.

Severe dementia.

Unwillingness to either complete the study requirements or to be randomised into control or intervention group.

Presence of neuromuscular disease or drugs affecting neuromuscular function.

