### Randomisation and blinding

As mentioned above, randomization will be done in a time-dependent manner (in four-week blocks) in order to avoid the confounding variable of participants in the control group seeing subjects in the treatment group performing physical activity in addition to normal hospital care. Participants will be explicitly informed and reminded not to discuss their randomisation assignment with assessment staff. The assessment staff will be blinded to participant randomisation assignment, as well as to the main study design and to what changes we expect to occur in the study outcomes in either group. Because blinding of assessment staff to participant randomisation assignment might not be actually feasible in all cases due to the time-dependent manner of randomisation, we will record blinding success and add it as a covariate in the analyses (see below). It will not be possible to conceal the group assignment from the staff involved in the training of the intervention group.

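### Admission date fixes the arm before consent is sought and eligibility judged, although Study design says assignment follows consent

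*Protocol article*

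**What the plan says.** Four parts of the protocol article bear on this.

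- **Order of events (Study design).** "After signing an informed consent form subjects will be randomly assigned (as explained below) to either the intervention or control group".
- **Unit of allocation (Study design).** "Patients admitted during four-week blocks of time will all be assigned to either the treatment or control group", with a one-week gap between blocks. Randomisation and blinding repeats the scheme. Both sections give its purpose: to keep controls from seeing other patients train.
- **Eligibility (Study participants and selection criteria).** Exclusions include "Any factor precluding performance of the physical training program or testing procedures as determined by the attending physician", followed by a list described as not exhaustive, and also "Unwillingness to either complete the study requirements or to be randomised into control or intervention group".
- **Blinding (Randomisation and blinding).** Blinding of assessment staff "might not be actually feasible in all cases due to the time-dependent manner of randomisation". Blinding success will be recorded and used as a covariate. Nothing is said about those who recruit or judge eligibility.

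Under Statistical analysis, the main test is a two-factor (group and time) repeated-measures ANOVA without covariates, repeated with blinding success, age, BMI, MMSE, previous falls and handgrip strength. Three-month falls, Katz and Barthel are compared by t test or Mann-Whitney test, and mortality by chi-square. Length of stay has no admission value.

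**The concern.** The stated order does not fit the design described. If the block decides the arm, nothing is left to assign after consent. The willingness criterion also presupposes that the patient does not yet know the arm.

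The wording matters because allocation is not concealed at enrolment. The trial runs in one geriatric department, with training up to three times a day. Once the first patient of a block is trained, or visibly is not, the arm of every later admission in that block can be known. A physician asked whether a frail patient can manage the training may answer differently when training is certain and when it is ruled out, and patients may consent differently too. The arms could then differ in frailty at entry, which randomising blocks does not prevent.

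**Working it through.** **1. The order of events.** Under the sentence on consent, the sequence is consent, then assignment. Under the block scheme, it is block assigned, admission, eligibility judgement, consent. Both cannot describe the same trial. Only the second fits the stated purpose of separating the arms in time.

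**2. The plan's own sample size.** Inputs: 60 per group and 20% loss (Sample size and statistical power). 60 / (1 − 0.20) = 75 per group, and 2 × 75 = 150. This reproduces the stated total. The power claim cannot be reproduced because no SD or baseline SPPB is given. At two-sided 0.05 and 80% power, 60 per group detects (1.960 + 0.842) × √(2/60) = 0.511 SD.

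**3. Number of blocks.** "The study will be performed between June 2012 and June 2013", and each cycle is 4 + 1 = 5 weeks.

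| Dates assumed | Weeks | Weeks / 5 | Complete four-week blocks |
|---|---|---|---|
| 30 June 2012 to 1 June 2013 | 48.0 | 9.6 | 9 |
| 1 June 2012 to 1 June 2013 | 52.1 | 10.4 | 10 |
| 1 June 2012 to 30 June 2013 | 56.3 | 11.3 | 11 |

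At 10 blocks, 150 / 10 = 15 patients are recruited per block.

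**4. Size of a selection effect (illustration).** Assume a normal admission score, and that the lowest fraction p is left out of training blocks only. The training-arm mean then rises by φ(z_p) / (1 − p) SD. The article gives no p, so a range is shown:

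- p = 5%: 0.103 / 0.95 = 0.11 SD
- p = 10%: 0.1755 / 0.90 = 0.195 SD
- p = 20%: 0.280 / 0.80 = 0.35 SD

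**5. What reaches the planned tests.** With two time points, the group-by-time test compares mean change. If the discharge score rises by b per unit of admission score, an admission offset δ shifts mean change by (b − 1)δ. This is zero at b = 1 and, for δ = 0.195, is −0.10 SD at b = 0.5 (b is assumed). A constant offset therefore cancels, and what remains can work against training. Selection on prospects of recovery could act either way.

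An outcome with no baseline term has no such cancellation. If it correlates r with the admission score, the shift is r × δ: 0.3 × 0.195 = 0.06 SD, or 0.5 × 0.195 = 0.10 SD (r is assumed). Length of stay and the three-month outcomes are of this kind.

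**6. Balance over the year (conditional).** If 10 blocks were drawn independently, a 7-3 or worse split would have probability 2 × (1 + 10 + 45 + 120) / 1024 = 0.34. If the split were forced to 5-5 without pairing, three given winter blocks would all fall in one arm with probability 2 × C(7,2) / C(10,5) = 42 / 252 = 0.17.

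**The case against.** The strongest reply has four parts.

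- **The sentence on consent points forward to an explanation, which follows in the same section.** No reader is misled about the unit of allocation. That is fair. But the pointer explains how patients are assigned and does not correct when.
- **A condensed article commonly leaves generation of the block sequence to the full protocol.** This stands. A reader might infer that the blocks are drawn by independent coin flips, that the arms will probably be uneven, or that two groups of 60 are at risk. The article does not say so. It describes no balancing over the year and rules none out, so the 34% holds only under independent draws.
- **The 0.195 SD is not a bias in the planned SPPB test.** This also stands. One might set it against the detectable difference (0.195 / 0.511 = 38%), but that compares an admission offset with an effect on change, and step 5 shows that the offset cancels wholly or in part. SPPB is also capped at 12, so fitter patients have less room to improve and even the direction is open.
- **Safeguards exist.** Several exclusions are concrete and apply to both arms, the ANOVA is repeated with covariates, and admission SPPB enters as the pre-test value. These help, but the adjusted analysis is only a repeat, and no adjustment is stated for the single-measurement three-month comparisons.

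**Conclusion.** The point holds in a limited form and should be corrected. The stated order contradicts the block scheme, and the scheme leaves allocation unconcealed while open eligibility and willingness criteria are applied. That recruiters know the arm is an inference, though a strong one in a single department. The article does not show that selection will occur.

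The possible size rests on assumption. A 10% exclusion in training blocks only gives an admission imbalance of about 0.19 SD (0.11 to 0.35 SD for 5% to 20%). Its effect on SPPB change is smaller and of uncertain sign. The more exposed results are length of stay, which is part of the major hypothesis, and three-month mortality, falls, Katz and Barthel. The seasonal point is secondary: balancing of the roughly 10 blocks (range 9 to 11) is not described, which is not evidence that it is absent.

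**What to change.** 1. In Study design, state that the four-week block is the unit randomised, before its patients are recruited. Release each block's assignment no earlier than its first day.
2. For every consecutive admission aged 75 or over, complete one fixed eligibility checklist, including the physician's judgement of fitness for training, whichever arm is current. For eligible consenting patients, complete the admission tests before the arm is disclosed. Withholding the arm from the patient does not hide it from recruiters, so the common checklist and the log in item 3 are the main protection.
3. Log and report screened, eligible, refused and enrolled patients by block and arm, so that differential selection can be seen.
4. Make the analysis adjusted for admission SPPB, age and MMSE the primary one. Apply the same adjustment to length of stay and the three-month outcomes, with a model suited to each. All three covariates are already collected.
5. If the sequence is not already balanced over the year, randomise within consecutive pairs of blocks, so that each ten weeks hold one block of each arm.

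The cost is a corrected sentence, a screening log, a changed order of analyses and possibly a new randomisation list. Pairing makes the second block of each pair predictable, but the arm becomes visible soon after any block starts. The block design and its protection against contamination are kept. These steps reduce and expose selection without fully concealing allocation.

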**Figure 1 F1:**
[figure not shown]
Study flow diagram.

All testing (at admission and discharge) will be performed in the same setting (*Hospital General Universitario Gregorio Marañón*, Madrid, Spain) and by the same investigators. The study will be performed between June 2012 and June 2013, following the ethical guidelines of the Declaration of Helsinki, last modified in 2000.

### Study participants and selection criteria

Participants will include approximately 150 elderly people aged 75 years or older recruited from patients admitted into the Geriatrics Department of the *Hospital General Universitario Gregorio Marañón* (Madrid, Spain). Due to the length of the study it is possible a patient will be readmitted after participating in either the experimental or control group. To avoid this confounding variable, a study participant who is readmitted to the hospital during the course of the study will not be included in the study population a second time.

The inclusion criteria are:

Age: 75 years or over.

Able to ambulate, with or without personal/technical assistance.

Able to communicate.

Informed consent: Must be capable and willing to provide consent.

The exclusion criteria are:

Duration of hospitalization < 72 hours

Any factor precluding performance of the physical training program or testing procedures as determined by the attending physician. These factors include, but are not limited to the following:

Terminal illness.

Myocardial infarction in the past 3 months.

Not capable of ambulation.

Unstable cardiovascular disease or other medical condition.

Upper or lower extremity fracture in the past 3 months.

Severe dementia.

Unwillingness to either complete the study requirements or to be randomised into control or intervention group.

Presence of neuromuscular disease or drugs affecting neuromuscular function.

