**Methods/Design:**

Patients aged 75 years or older admitted for a short hospital stay (≤14 days) will be randomly assigned to either a usual care (control) group or an intervention (training) group. Participants allocated in the usual care group will receive normal hospital care and participants allocated in the intervention group will perform multiple sessions per day of lower limb strength training (standing from a seated position) and walking (10 min bouts) while hospitalized. The primary outcome to be assessed pre and post of the hospital stay will be functional capacity, using the Short Physical Performance Battery (SPPB), and time to walk 10 meters. Besides length of hospitalization, the secondary outcomes that will also be assessed at hospital admission and discharge will be pulmonary ventilation (forced expiratory volume in one second, FEV_1_) and peripheral oxygen saturation. The secondary outcomes that will be assessed by telephone interview three months after discharge will be mortality, number of falls since discharge, and ability to cope with activities of daily living (ADLs, using the Katz ADL score and Barthel ADL index).

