### Objectives

The purpose of the proposed research [acronym: AGECAR (Activity in GEriatric Acute CARe)] is to investigate the effect of an intrahospital multi-time per day physical training program, consisting of walking and strength training of the lower limbs, during a short period of hospitalization in seniors aged 75 years or older on functional capacity at discharge (primary outcome). The effect of the physical training program will be compared to a control group receiving normal hospital care. Besides length of hospitalization, the secondary outcomes that will also be assessed at hospital admission and discharge will be pulmonary ventilation (forced expiratory volume in one second, FEV_1_) and peripheral oxygen saturation. The secondary outcomes that will be assessed by telephone interview three months after discharge will be mortality, number of falls after discharge, and ability to cope with activities of daily living (ADLs, using the Katz ADL score and Barthel ADL index).

Increased age and a history of falls in the previous year are associated with decreased functional capacity [11], and handgrip strength is a predictor of survival [20] and mobility [21]. On the other hand, low cognitive ability, reflected as low scores on the Mini-Mental Status Examination (MMSE) is associated with increased chance of decreased functional capacity upon discharge [11,22]. Thus, we will also determine if age, history of falls in the previous year, handgrip strength and MMSE scores (covariates) will have an influence on the effects of the training program on the aforementioned primary and secondary outcomes. The major hypothesis is the prescribed training program will increase functional capacity at discharge while decreasing length of hospitalization.

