### Intervention (training)

The intervention will consist of strength training of the lower body and walking. Both types of training will be performed three times per day during the week (Monday to Friday), two times per day on Saturday, beginning as soon as possible after admission and continuing until discharge. No training will take place on Sunday. Training sessions will be dispersed throughout the day. When three sessions per day are performed, one will take place between 9–11 a.m., one between 13–15 p.m., and the last one between 17–19 p.m.; when two sessions per day are performed training will take place during the first two of the aforementioned time periods. Strength training will be performed first, and followed by walking. A rest period of up to five minutes will be allowed between the strength and walk training.

Strength training will consist of rising from a seated position in a chair to an upright position with or without the use of the subject’s hands on the armrests of the chair. Initially 10 repetitions or as many repetitions as possible up to 10 of rising from a seated position will be performed each training bout. The strength training will be progressed from one set of the 10 repetitions to 2 and then 3 sets of the 10 repetitions based on individual progress. When a patient can perform one set of 10 repetitions for all three training bouts on two consecutive days a second set will be added. When a patient can perform two sets of 10 repetitions for all three training bouts on two consecutive days a third set will be added.

Completion of one set of 10 repetitions of strength training should take approximately one-two minutes. A two-minute rest period will be allowed between strength training sets if more than one set is performed. If a subject completes three sets of strength training total training time will be between 7 and 10 minutes.

Walk training will consist of walking as far as possible with or without assistance for 10 minutes. Total length of each training session will be 20–23 minutes. During the week when three training sessions per day are performed total training time per day will be 60–69 minutes. On Saturdays when two training sessions per day are performed total training time will be 40–46 minutes. All training sessions will be individually monitored with a record of training completed compiled.

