### Statistical analysis

To assess the training effects on the study outcomes, we will analyze the data according to the intention-to-treat principle [37]. When post-test data are missing, baseline scores will be considered post-test scores. We will use a two-factor (group and time) analysis of variance (ANOVA) with repeated measures. We will repeat the analysis using the actual blinding of assessment staff to participant randomisation assignment (successful or not), baseline values of age, body mass index, MMSE, number of falls within the previous year and handgrip strength as covariates. For each outcome variable we will report the level of significance corresponding to the main group (between-subjects), time (within-subjects) and interaction (group × time) effects. We will perform post hoc pre- vs. post comparisons by group only when a significant group*time effect is present. The level of significance will be set to = 0.05. We will adjust multiple comparisons for mass significance [38]. We will use the Student’s *t* test (or its non-parametric equivalent, the Mann Whitney’s *U* test) for comparing between the two groups the mean values of those secondary outcomes that will be assessed only once, i.e. three months after discharge (number of falls, Katz score and Barthel index). We will compare mortality rate at three months after discharge in the two groups with the chi square test.

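### The 72-hour exclusion is worded as actual stay, which is known only after the arm is set; applied as written it conflicts with intention-to-treat and can attenuate the length-of-stay comparison

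*Protocol article*

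**What the plan says.** All references are to the protocol article.

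- **Study participants and selection criteria** lists among the exclusions "Duration of hospitalization < 72 hours". It does not mention an expected or anticipated stay.
- **Study design** fixes the arm by calendar period: "Patients admitted during four-week blocks of time will all be assigned to either the treatment or control group". On sequence it says "After signing an informed consent form subjects will be randomly assigned". No 72-hour wait before consent, baseline testing or assignment is described.
- **Intervention (training)** schedules the sessions as "beginning as soon as possible after admission and continuing until discharge".
- **Objectives** states the direction expected for stay: "The major hypothesis is the prescribed training program will increase functional capacity at discharge while decreasing length of hospitalization". Length of hospitalization is also listed under Secondary outcome measures.
- **Statistical analysis** says "we will analyze the data according to the intention-to-treat principle", with the baseline score standing in for a missing post-test score.
- **Abstract, Methods/Design** adds an upper limit that the selection criteria do not repeat: "Patients aged 75 years or older admitted for a short hospital stay (≤14 days) will be randomly assigned".

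**The concern.** Whether a patient meets the criterion is settled at 72 hours, or at discharge if that comes first. By then the arm is set, baseline has been measured and, in a training block, sessions may have begun. The criterion is therefore a post-allocation event, and one that the trial expects its treatment to move.

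Two things are at stake. First, removing allocated patients for a short stay is not an intention-to-treat analysis. Carrying the baseline forward does not help, because that rule applies to patients who are in the analysis with a missing post-test, not to patients who have been excluded. Second, length of stay is an outcome. If training brings some discharges forward to before 72 hours, those patients leave the training arm's data while comparable control patients remain, and the difference in stay is cut at its short end. The primary SPPB comparison could also be affected, through any link between stay and recovery.

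**Working it through.** **The plan's own figure.** Sample size and statistical power gives two groups of 60 and a 20% loss: 120 / (1 − 0.20) = 150, which reproduces. If post-allocation exclusions came on top of that loss, keeping 120 evaluable would need 120 / (0.8 × 0.9) = 167 recruits with 10% dropped, or 120 / (0.8 × 0.8) = 188 with 20% dropped. Both drop rates are assumptions.

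**Effect on length of stay: inputs.** The article gives no stay distribution for this trial. Its Background cites earlier cohorts with average stays of 5–8 days. The following are assumed: log-normal stay L in controls with mean 7 and SD 4 days, and a 15% shortening under training.

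**Formulas.**

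- s² = ln(1 + (4/7)²) = 0.2826, so s = 0.5316.
- Controls: μ = ln 7 − s²/2 = 1.8046. Training: μ = 1.8046 + ln 0.85 = 1.6421.
- Share excluded: p = Φ((ln 3 − μ)/s).
- Mean stay among those kept: mean × Φ((μ + s² − ln 3)/s) / (1 − p).

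**Effect acting from admission.**

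- Controls: p = Φ(−1.328) = 9.2%; mean kept = 7 × 0.9685 / 0.9079 = 7.47 days.
- Training: p = Φ(−1.022) = 15.3%; mean kept = 5.95 × 0.9399 / 0.8467 = 6.60 days.
- True difference: 7 − 5.95 = 1.05 days. Difference after exclusion: 0.86 days. Share kept: 0.86 / 1.05 = 82%.
- Extra exclusions per 75 trained patients: (0.153 − 0.092) × 75 ≈ 5.

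**Sensitivity to when the effect starts.** The distribution is the same, but the 15% shortening acts only on time after day d: a stay L > d becomes d + 0.85 × (L − d).

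| Effect starts | Excluded, control v training | True difference (days) | Difference after exclusion (days) | Share kept |
|---|---|---|---|---|
| At admission | 9.2% v 15.3% | 1.05 | 0.86 | 82% |
| After day 1 | 9.2% v 13.2% | 0.90 | 0.80 | 89% |
| After day 2 | 9.2% v 11.1% | 0.75 | 0.74 | 99% |
| After day 3 | 9.2% v 9.2% | 0.61 | 0.67 | not attenuated |

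In the last row the same patients are excluded in both arms. The difference is then simply that among longer stayers: 0.61 / (1 − 0.092) = 0.67.

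**Sensitivity to the distribution.** With the effect acting from admission, control means of 5 to 8 days, coefficients of variation of 0.5 to 0.7 and shortenings of 10% to 30%, the share of the true difference kept runs from 67% to 90%. With no effect on stay, both arms lose equal shares and the contrast is unbiased.

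**SPPB.** The assumptions are no true SPPB effect, a correlation of −0.2 or −0.4 between SPPB change and log stay, mean stay 6 or 8 days, coefficient of variation 0.6, and shortenings of 10% to 30% from admission. Selection alone then shifts the comparison by −0.01 to −0.12 SD, against training. Reversing the correlation reverses the sign.

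**The case against.** The strongest reply is that nobody is shown to be removed after allocation. The line sits in a list of selection criteria, beside items judged by the attending physician, and the abstract's phrase about admission for a short stay can be read as an anticipated stay. The analysis section removes no one. The flow diagram, which might show where the criterion is applied, is not available, and the article condenses a fuller protocol. Read as an expected stay, the criterion would be harmless. This stands in part: a proven breach of intention-to-treat cannot be claimed, only that the text as written leads to one and nothing in it says otherwise.

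The reply on size also stands. Differential exclusion needs an effect on discharge within the first 72 hours, which the article does not claim. The resulting bias in stay would understate the hypothesised benefit, not create a false one.

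Two stronger readings are tempting and unsupported:

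- **That the training arm loses its best responders and the SPPB result is biased.** Early discharge may reflect mild illness with little room to gain on a 0–12 scale, not response to training. The direction cannot be settled from the article.
- **That the difference in stay is roughly halved.** On the same assumptions, cutting at 3 and at 14 days takes 1.05 days down to 0.55. But the 14-day limit is absent from the selection criteria, and nothing says that it is applied to actual stay.

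**Conclusion.** The point holds in a limited form. The wording makes eligibility depend on an actual, post-allocation stay that the trial hopes to shorten. Excluding allocated patients on it contradicts the article's own analysis principle. That conflict rests on the text alone and needs no model.

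The numerical consequence is conditional. In the worked case the length-of-stay difference keeps 82% of its true value if training acts from admission. It is not attenuated, and exclusions are equal, if training acts only after day 3. These figures rest on an assumed log-normal stay and an assumed 15% shortening. For SPPB, the most that can be said is that a bias is possible, indirect, probably small and of unknown sign.

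Length of stay also has no admission value, so the group × time ANOVA cannot be fitted to it, and it is not among the outcomes named for the once-only tests. That is a separate, secondary point.

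**What to change.** 1. State that every allocated patient is kept in the primary and length-of-stay analyses whatever the actual stay, with the subset staying 72 hours or more shown only as supplementary.
2. If a minimum stay is wanted for eligibility, word it as an expected stay recorded at admission, where possible by someone unaware of the block's arm. Because whole blocks share one arm and it may be known, keep a log of all screened patients by block.
3. Reconcile the abstract's 14-day limit with the selection criteria, and do not apply it to actual stay after allocation.
4. Name a once-only between-group test for length of stay.

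**Cost.** These are changes to eligibility wording and a sentence or two of analysis, plus the screening log. The planned 150 need not change. A few short-stay patients with little training will slightly dilute the SPPB effect. An expected-stay judgment carries some risk of selective enrolment when the arm is known; the log makes this visible but does not remove it.
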